### Assessment accuracy of the VOC sensing techniques (GC-tof–MS, SIFT-MS)

The primary outcome of the prospective cohort study is assessed in two ways, namely by comparing the VOCs data of the two VOCs-sensing techniques (GC-*tof*–MS and SIFT-MS) at inclusion of all participating children (both wheezing preschool children and healthy controls) to the final diagnosis at six years of age, and by comparing the VOCs-data of the SIFT-MS at the baseline visit to the results of the gold standard (GC-*tof*–MS) at the baseline visit. The sensitivity, specificity, positive predictive value and negative predictive value for a diagnosis of asthma of the two different VOCs sensing techniques (GC-*tof*–MS and SIFT-MS) will be determined with corresponding 95% confidence intervals. Statistical analysis of the volatilome will be performed by current published standards on data analysis for VOCs analysis in breath [51]. The extensive VOCs data derived from the mass spectrometry analyses will be implemented in an algorithm by using mathematical models for analysis of sensor signals (for instance neuronal networks, random forest, support vector machine, or principle component analysis) as described previously [37].

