## Background

Respiratory symptoms, such as wheeze, breathlessness, chronic cough, and sputum production, are very common in young children. Around 40% of all children under the age of 6 suffer from these asthma-like symptoms [1, 2]. Although asthma is the most prevalent chronic disease in children, only the minority (around 30%) of preschool children with recurrent wheeze have persistent wheeze and asthma in later life [1–3]. The majority of wheezing preschool children has transient, viral infection-induced symptoms without an increased risk for asthma and most of the time no need for asthma medication (so called ‘transient wheeze’ or ‘viral wheeze’). At present, there is no proper clinical instrument available that can discriminate between ‘persistent wheeze’ (children with asthma) and ‘transient wheeze’ (children without asthma) at preschool age.

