
### Objectives of the new study: the ADEM2 study

The previous ADEM study generated a lot of insight in the diagnostic potential of VOC patterns in exhaled breath with respect to an early diagnosis of asthma, and in multiple potential underlying pathophysiological mechanisms leading to the development of asthma. However, since then, many new questions arose. For example with regards to the feasibility of bringing the assessment of VOCs in exhaled breath into daily clinical practice, and with respect to the impact an early diagnosis of asthma will have on wheezing preschool children and their parents. Also, recent developments in the evolving field of multi-omics generated new approaches to investigate the early pathogenesis of asthma. Therefore, a new randomised controlled trial and prospective study in wheezing preschool children was designed, the ADEM2 study.

The primary objective of the ADEM2 study is to prove health gain and reduction in costs by application of a point-of-care (POC) breath test for an early asthma diagnosis in preschool children. A multicentre randomised controlled trial (RCT) in 220 wheezing preschool children will be performed. Children will be randomised into an intervention group (*n* = 110) in which the doctors and parents will be informed about the predicted asthma diagnosis provided by the breath test, or into a usual care group (*n* = 110) in which all parties are masked for the predicted diagnosis. The second objective is to further develop and validate a reliable, non-invasive point-of-care breath test. In a prospective observational study we will assess feasibility, accuracy and reproducibility of the innovative VOC techniques (e.g. SIFT-MS and VOC sensors) in comparison with the gold standard breath test (GC-tof–MS), for an early asthma diagnosis in wheezing preschool children. The third and final objective of the ADEM2 project is to combine metabolomic, immunological, (epi)genomic, transcriptomic, and microbiome data to unravel potential important pathways for asthma development. Moreover, the utility of predictive, multi-omic testing of childhood asthma in wheezing pre-school children will be explored. This knowledge can offer clues for novel diagnostic tests and proper or even revised treatment (e.g. microbiota-based therapy) in wheezing children.

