### Exclusion criteria

Wheezing children: presence of chronic and/or inflammatory disease other than asthma (e.g. inflammatory bowel disease, auto-immune disorders, cardiac disease, congenital lung disease, kidney or liver disease), prematurity < 35 weeks gestational age, postnatal need for oxygen, CPAP, non-invasive or invasive ventilation, or mental disability.Healthy children: a history of asthma or wheeze, other chronic and/or inflammatory disease other than asthma (e.g. inflammatory bowel disease, auto-immune disorders, cardiac disease, congenital lung disease, kidney or liver disease), prematurity < 35 weeks gestational age, postnatal need for oxygen, CPAP, non-invasive or invasive ventilation or mental disability.

Children with a recent course of systemic corticosteroids or antibiotics are not excluded from participation, but the baseline visit will be postponed until at least one month after the treatment.

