### Prospective cohort study

Secondary outcomesThe sensitivity and specificity of new VOC sensing techniques (e.g. SIFT-MS and VOC sensors) for a diagnosis of asthma or transient wheeze in preschool children. Assessment at the start of the study in relation to the current gold standard in breath research (GC–MS) and at the age of 6 years in relation to the final diagnosis.Identification of other potential discriminating biological parameters (such as allergic sensitisation, immunological markers, epigenetics, transcriptomics, microbiome) between asthma, transient wheeze, and healthy controls, and the subsequent identification of underlying disease pathways and relation to the discriminative VOCs in exhaled breath. Assessment of data collected at the start of the study and at the end in relation to the final diagnosis at the age of 6 years.Identification of discriminative exhaled VOCs (based on GC-*tof*–MS analysis) between children with asthma, children with transient wheeze and healthy children. Assessment of data collected at the start of the study and at the end of the study in relation to the final diagnosis at the age of 6 years.

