### Lung function

*Airway resistance test:* the airway resistance will be measured annually by means of the TremoFlo C-100™(Thorasys, Montreal, Canada) using the flow-oscillation technique (http://thorasys.com). The children will sit upright with their head in a neutral position and the researcher standing behind them to manually support the cheeks to minimise the upper airway shunt. The child will be asked to breathe quietly with the mouthpiece into his or her mouth, while making a seal with the lips around the mouthpiece and wearing a nose clip. The measurements will be repeated until at least three, artefact free measurements are completed. Thereafter, 300 µg of salbutamol will be inhaled via the Aerochamber®. After 15 min, the airway resistance measurements are repeated to assess the reversibility to a beta-2 agonist.

*Spirometry, bronchial NO and bronchial hyperresponsiveness:* additional lung function tests are performed during the final visit at age six years in order to make a definite asthma diagnosis in all participating children. These tests are performed and selected according to the ERS clinical practice guidelines for the diagnosis of asthma in children [38]. Spirometry and bronchodilator reversibility (BDR) testing is performed in which the highest forced expiratory volume in one second (FEV1), forced vital capacity (FVC), and maximal expiratory flow at 50% FVC (MEF50) of three technically satisfactory MEFV curves will be used for analysis. Also, in all children the fraction of exhaled nitric oxide (FeNO) will be measured with an online single breath technique with constant expiratory flow (NIOX VERO ®, Circassia AB, Oxford, UK). The Fractional exhaled NO (FeNO) value will be expressed as parts per billion. Only in a subset of patients in which a conclusive asthma diagnosis cannot be made based on spirometry, BDR and FeNO, a direct bronchial challenge test will be performed by administrating aerosols of methacholine.

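### As worded, breath-test accuracy against the age-6 diagnosis pools healthy controls with wheezing children, so NPV is overstated, PPV is distorted, and specificity depends on how healthy children test

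*Protocol article*

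**What the plan says.** The protocol article's section on the accuracy of the VOC sensing techniques sets out two comparisons. One sets baseline SIFT-MS against baseline GC-tof-MS. The other, at issue here, sets the VOC data of both techniques "at inclusion of all participating children (both wheezing preschool children and healthy controls) to the final diagnosis at six years of age". The next sentence promises "The sensitivity, specificity, positive predictive value and negative predictive value for a diagnosis of asthma of the two different VOCs sensing techniques", with 95% confidence intervals, and names no narrower population.

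Other sections describe the purpose more narrowly:

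- The objectives say the techniques are assessed "for an early asthma diagnosis in wheezing preschool children".
- The cohort outcomes describe accuracy "for a diagnosis of asthma or transient wheeze in preschool children", and Table 2 uses the same two-way contrast with a probability score above 0.5 read as asthma.
- The section on the diagnosis at 6 years allows two results, transient wheeze or asthma. A child who never wheezed fits neither.
- The exclusion list for healthy children begins with "a history of asthma or wheeze, other chronic and/or inflammatory disease other than asthma".

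The healthy children do receive a reference diagnosis: the lung function section says the age-6 tests are done "in order to make a definite asthma diagnosis in all participating children". Pooling them is therefore feasible as well as written.

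Table 2 assigns diagnostic value to analysis group V, and the comparison that names healthy controls to groups 0 and V. Fig. 5, which defines the groups, is not shown.

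**The concern.** A child with no history of wheeze would not be a candidate for this test. Including such children changes the question from asthma versus transient wheeze to asthma versus a mixture of transient wheeze and health. The proportions of that mixture come from recruitment, not from any clinical population. PPV and NPV depend directly on case mix, and specificity becomes a weighted average over two kinds of non-asthmatic child.

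The accuracy section and Table 2 call this the cohort's primary outcome, although the outcomes section lists it under secondary outcomes. It will inform whether SIFT-MS can stand in for GC-tof-MS, which the article itself regards as poorly suited to routine clinical use. NPV matters most, because it tells a clinician how far a transient wheeze result can be relied on. Pooled figures would also not be comparable with the benchmark of 84% and 82%, which came from a study of 202 wheezing children.

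**Working it through.** **The plan's own figure.** The article gives no sample size or precision calculation for test accuracy, so there is none to reproduce. What follows illustrates the effect of pooling using the article's planning values.

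**Inputs from the article**
- Wheezing children: 220 planned with 10% dropout (Sample size), so 220 × 0.9 = 198.
- Asthma among them: 30%. The Background says "only the minority (around 30%) of preschool children with recurrent wheeze have persistent wheeze and asthma in later life".
- Sensitivity 84% and specificity 82% in wheezing children (earlier ADEM study). These belong to clinical information combined with VOCs, so they are planning values only.

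**Assumptions**
- H, the number of healthy controls. The article gives no total, only 40 in the eosinophil subset. Range used: 40 to 220.
- s, the proportion of healthy children who test negative. The article gives no value. Range used: 0.70 to 1.00.
- No control develops asthma by age 6 (relaxed below).

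**Wheezing children only**
- Asthma: 198 × 0.30 = 59.4. TP = 0.84 × 59.4 = 49.9; FN = 9.5.
- Transient wheeze: 138.6. TN = 0.82 × 138.6 = 113.7; FP = 24.9.
- PPV = 49.9 / (49.9 + 24.9) = 66.7%. NPV = 113.7 / (113.7 + 9.5) = 92.3%.

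**Pooled with H controls**
- Specificity = (TN + H·s) / (TN + FP + H)
- PPV = TP / (TP + FP + H·(1 − s))
- NPV = (TN + H·s) / (TN + H·s + FN)
- Sensitivity = TP / (TP + FN), unchanged at 84%

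With H = 80 and s = 0.95, specificity = (113.7 + 76) / 218.6 = 86.8%, and NPV = 189.7 / (189.7 + 9.5) = 95.2%. Asthma prevalence in the set is 59.4 / 278 = 21.4%.

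Varying s at H = 80:

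| s | Specificity | PPV | NPV |
|---|---|---|---|
| Wheezing only | 82.0% | 66.7% | 92.3% |
| 1.00 | 88.6% | 66.7% | 95.3% |
| 0.95 | 86.8% | 63.3% | 95.2% |
| 0.90 | 84.9% | 60.2% | 95.1% |
| 0.82 | 82.0% | 55.9% | 95.0% |
| 0.70 | 77.6% | 50.5% | 94.7% |

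Varying H at s = 0.95:

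| H | Specificity | PPV | NPV |
|---|---|---|---|
| 40 | 84.9% | 64.9% | 94.1% |
| 110 | 87.8% | 62.1% | 95.8% |
| 220 | 90.0% | 58.1% | 97.1% |

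**Robustness** (220 wheezing children, H = 80, s = 0.95)
- If 5% of controls develop asthma, specificity is 86.3%, PPV 65.1% and NPV 94.7%.
- If true specificity in wheezing children is 60%, pooling lifts it to 72.0%, and NPV from 89.7% to 94.1%. A weaker test gains more.

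**Precision of specificity** (normal approximation)
- Wheezing only: 1.96 × √(0.82 × 0.18 / 138.6) = 6.4 points.
- Pooled, H = 80, s = 0.95: 1.96 × √(0.868 × 0.132 / 218.6) = 4.5 points.
- Ratio: 6.4 / 4.5 ≈ 1.4.

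**The case against.** The strongest reply is that the analysis set may not be what it seems. The phrase naming all children says whose VOC data are compared with the diagnosis, while the sentence introducing the four accuracy measures names no population. Table 2 lists healthy controls explicitly only in the row assigned to groups 0 and V, so group V alone, used for accuracy, might be wheezing children only. This stands as an uncertainty. It does not settle the matter, because Table 2 also gives VOC identification to group V, and the outcomes section describes that work across asthma, transient wheeze and healthy children. If V is wheezing-only, the accuracy section contradicts Table 2; if not, pooling is planned. The text needs correcting either way. Nor is this a detail left to an analysis plan, since the article states the population.

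A reader might also infer that pooling inflates accuracy across the board, so that no reported figure would apply to a wheezing child. The documents do not support that. Sensitivity is unchanged if no control develops asthma. PPV moves against the test whenever a control tests positive. A rise in specificity requires healthy children to test negative more often than transient wheezers. That is plausible given how controls are selected, but the article reports no breath-test result in healthy children; at s = 0.82 specificity does not move, and at s = 0.70 it falls.

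**Conclusion.** The concern holds for the text as worded. Pooling makes the predictive values describe a case mix set by control recruitment. NPV is overstated in every scenario tried, by about 3 points with 80 controls. PPV is distorted, usually downward, and falls if any control tests positive. Specificity is overstated by about 5 to 7 points with 80 controls if 95–100% of them test negative, unaffected if they test negative as often as transient wheezers, and understated if less often. Sensitivity is essentially unaffected.

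These sizes rest on 30% prevalence and 84%/82% accuracy in wheezing children, and on assumed values for the number of controls and their negative rate. Whether Table 2 already restricts the set cannot be checked without Fig. 5. The randomised comparison is not affected.

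**What to change.** State in the accuracy section that sensitivity, specificity, PPV and NPV against the age-6 diagnosis are estimated primarily in wheezing children, asthma versus transient wheeze, and make the definition of group V in Table 2 and Fig. 5 agree. Report the false-positive rate in healthy children as a separate figure. Keep the healthy children for VOC discovery and for SIFT-MS versus GC-tof-MS agreement at baseline, where including them is reasonable.

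This takes about one sentence and no new data. The price is a less favourable NPV, probably a less favourable specificity, and a specificity interval about 40% wider: a half-width of about 6.4 rather than 4.5 points with 80 controls.

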### Hypotheses of the ADEM2 study

The hypothesis of the clinical trial of the ADEM2 study is that application of the breath test in preschool children with asthma-like symptoms will result in important health gain and reduction of costs of care. In children with asthma, we expect that an early diagnosis by the breath test will result in more targeted and better treatment. This will facilitate better asthma control, improved lung function, less exacerbations, less hospital admissions, improved quality of life, and probably less airway remodelling. In children with transient wheeze, we hypothesise that an early diagnosis will diminish uncertainty of parents and treating doctors, with less referrals, less additional examinations (X-rays, allergy tests, microbial cultures or viral PCR tests), and less ineffective treatment (antibiotics, corticosteroids, or antihistamines). Parents will be reassured by the early diagnosis of transient wheeze, which will probably increase quality of life and decrease medical consumption. In both cases, cost savings are expected because of a proper diagnosis by the breath test due to significantly reduced hospital based care and medication use in children with transient wheeze, and prevention of undertreatment related sequela in children with asthma.

Our hypothesis of the observational cohort study with respect to the feasibility, reproducibility and accuracy of the alternative VOC-sensing techniques is that innovative techniques such as SIFT-MS are not inferior to the current golden standard GC–MS. We also hypothesise that new (combinations of) biomarkers will be found that improve the diagnostic accuracy to identify the wheezing preschool child developing asthma, such as epigenetic signatures of blood eosinophils, microbiome data of both nasopharyngeal swabs and faecal samples, whole RNA sequencing on blood, gene-expression of relevant asthma genes, and immunological markers.

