**Fig. 4 Fig4:**
[figure not shown]
Breath collection in a child using a tailored breath sampling system (see insert)

*SIFT-MS analysis:* the sampling bag will be connected to the Syft Voice 200 Ultra (Syft technologies, Christchurch, New Zealand) for SIFT-MS analysis of the breath. The instrument will be applied in full spectral mass scan mode in the mass-to-charge ratio (m/z) range of 15–250 amu for all three precursor ions (H3O^+^, NO^+^, O2^+^). Three acquisition repeats will be performed in a single run and the full scan data (ion counts per second) will be averaged over the three repeats for each m/z value. The SIFT-MS measurement uses approximately 60 ml of exhaled breath.

*GC-tof–MS analysis* the remaining breath in the sampling bag will be emptied across a stainless steel, two-bed sorption tube filled with Carbograph 1 TD/Carbopack™ X (Markes International, Llantrisant, UK) for rapid adsorption and stabilisation of volatile compounds. The tubes are airtight capped and stored at 4 °C until analysis. During the analysis, VOCs are first released from the tube using thermal desorption (Unity desorption unit; Markes International) at 270 degrees Celsius. In the next step, 25% of the mixture of vapour is loaded onto a cold (5 °C) sorption trap, while the remaining 75% of the mixture is recollected into an identical sample tube. The vapour mixture was then reloaded from trap into the gas chromatography time-of-flight mass spectrometry (Tempus Plus; ThermoFischer Scientific) (GC-tof–MS) analysis. The temperature of the GC was programmed as follows: first 40 °C for 5 min then it was increased by 10 °C every minute until 270 °C is reached. This temperature is maintained for 5 min. Electron ionisation at 70 eV was used with 5 Hz scanning rate over a range of m/z 35–350 [36]. The pre-processing of the raw GC-*tof*–MS spectra consists of noise removal, baseline correction, alignment, and peak detection. Thereafter, complementary compounds in different samples are linked, based on similarity of retention times and mass spectra. The area under the peak will be calculated for each compound. To make the spectra comparable, normalisation to the total area will be performed [37].

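### The SIFT-MS non-inferiority hypothesis has no matching analysis: the plan names a separate interval for each technique, with no paired difference and no margin

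*Protocol article*

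**What the plan says.** In the protocol article, *Hypotheses of the ADEM2 study* commits the cohort study to a non-inferiority hypothesis on feasibility, reproducibility and accuracy: "innovative techniques such as SIFT-MS are not inferior to the current golden standard", meaning GC–MS.

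*Assessment accuracy of the VOC sensing techniques* assesses this outcome in two ways.

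- **Against the age-6 diagnosis.** Sensitivity, specificity, PPV and NPV of each technique "will be determined with corresponding 95% confidence intervals". Table 2 repeats these accuracy measures, with one cut-off (probability score above 0.5) for both techniques. It lists the outcome as primary for the cohort.
- **Against each other at baseline:** "by comparing the VOCs-data of the SIFT-MS at the baseline visit to the results of the gold standard". No statistic, interval or criterion is attached.

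The two measurements are paired by design. The *Volatile Organic Compounds* section runs SIFT-MS from the sampling bag first, and then, for GC-tof-MS, "the remaining breath in the sampling bag will be emptied across" a sorption tube.

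On modelling, the article says: "The extensive VOCs data derived from the mass spectrometry analyses will be implemented in an algorithm by using mathematical models". The model family is left open ("for instance neuronal networks, random forest, support vector machine, or principle component analysis"), and the details are referred to earlier publications.

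The article gives no margin, no interval for a difference and no sample size for this hypothesis.

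**The concern.** Non-inferiority is a statement about a difference: SIFT-MS may be worse than GC-tof-MS, but by less than an agreed amount. Testing it needs an interval for that difference and a margin to set it against. Two separate intervals supply neither. They show how precisely each technique was measured, and they leave out the within-child correlation that a shared breath sample creates.

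This goes beyond detail left to a later document. The article chooses an inference for the accuracy outcome, and that inference does not answer the hypothesis it states. At stake is the second objective, developing and validating a faster point-of-care test. A claim that SIFT-MS can stand in for GC-tof-MS would have no defined evidential standard behind it.

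**Working it through.** **The plan's own figure.** The only computed sample size is for the RCT: 20% against 40%, alpha 0.05, power 80%, 91 per group. The two-proportion formula gives 82 per group without continuity correction and 91 with it, so 91 reproduces. Allowing 10% dropout gives 182/0.90 = 203, below the planned 220. The 70 to 80 quoted for the cohort concerns omics work. Neither figure addresses the accuracy comparison.

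**Inputs**

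- Wheezing children: 220, or 220 × 0.90 = 198 after the stated dropout (*Sample size*).
- Share with asthma at age 6: around 30% (*Background*), assumed to apply here. This gives 59 to 66 cases. A 20 to 40% range gives 40 to 88.
- Sensitivity: 84%, from the earlier ADEM study. That figure combined clinical information with VOCs, so using it for either technique is an assumption.
- Discordance, the share of asthma cases that the two techniques classify differently: not in the article. I assume 10, 15 and 20%. Independent classifications would give 2 × 0.84 × 0.16 = 26.9%.

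**Interval half-widths for sensitivity (percentage points)**

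| Quantity | Formula | 59 cases | 66 cases |
|---|---|---|---|
| One technique | 1.96 × √(0.84 × 0.16/n) | 9.4 | 8.8 |
| Difference, treated as independent | 1.96 × √(2 × 0.84 × 0.16/n) | 13.2 | 12.5 |
| Paired difference, 10% discordance | 1.96 × √(0.10/n) | 8.1 | 7.6 |
| Paired difference, 15% discordance | 1.96 × √(0.15/n) | 9.9 | 9.3 |
| Paired difference, 20% discordance | 1.96 × √(0.20/n) | 11.4 | 10.8 |

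The paired rows take the true difference as zero. At 40 and 88 cases the one-technique half-width is 11.4 and 7.7 points.

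**Power of a paired non-inferiority test on sensitivity** (one-sided 0.025, no true difference): Φ(margin/√(discordance/n) − 1.96). Cases needed for 80% power: discordance × (1.96 + 0.84)²/margin². The margins are assumptions.

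| Margin | Power at 59 cases (discordance 10/15/20%) | Cases for 80% power |
|---|---|---|
| 5 points | 23 / 17 / 14% | 314 / 471 / 628 |
| 10 points | 68 / 51 / 40% | 79 / 118 / 157 |
| 15 points | 95 / 84 / 73% | 35 / 53 / 70 |

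At 66 cases and a 10-point margin, power is 73 / 55 / 44%.

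Specificity is less limiting. Among 139 wheezing children without asthma (198 − 59), power at a 10-point margin is 96 / 86 / 75%. The accuracy analysis also includes healthy children, whose total the article does not give.

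**The case against.** The strongest reply is that per-technique accuracy with intervals is ordinary diagnostic reporting, and that a margin and a paired method commonly sit in an analysis plan. The article also has a second route that compares the techniques directly in the same children. Part of this stands. The absence of a margin alone would be a weak point, and it would be wrong to say that the pairing is ignored throughout. But the direct comparison has no statistic or criterion. Agreement with GC-tof-MS is also a different quantity from accuracy against the age-6 diagnosis. The one inference that is specified still does not fit the hypothesis.

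A reader might infer three stronger things that the article does not support.

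- **That non-inferiority will be declared from overlapping intervals.** No such rule, or any decision rule, is stated.
- **That the SIFT-MS algorithm will be scored in the children it was trained on.** The article is silent on training and validation and defers to cited work: "Statistical analysis of the volatilome will be performed by current published standards on data analysis for VOCs analysis in breath". Cross-validation or a held-out set may be specified elsewhere.
- **That the comparison favours SIFT-MS** because GC-tof-MS already has a rule from the earlier cohort. The text sends the mass spectrometry data into an algorithm without singling out SIFT-MS. Table 2 applies one cut-off to both, and identifying discriminative VOCs by GC-tof-MS is itself a cohort outcome. GC-tof-MS may therefore be re-modelled too, and the direction of any bias cannot be determined.

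**Conclusion.** The point holds as a mismatch between hypothesis and analysis. The article claims non-inferiority but specifies separate intervals for accuracy, gives no margin, and leaves its direct comparison without a criterion.

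The size is moderate. Pairing narrows the interval for the difference in sensitivity from about ±12.5 to 13 points to about ±8 to 10 points, if 10 to 15% of cases are discordant. At 20% discordance the gain shrinks, to about ±11. These figures rest on 30% asthma, 84% sensitivity for both techniques and the assumed discordance.

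The correct analysis does not rescue the hypothesis by itself. With about 59 cases, a 10-point margin has roughly 40 to 68% power and a 5-point margin 14 to 23%. The RCT comparison is not affected.

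**What to change.** 1. Make the accuracy comparison the paired difference, SIFT-MS minus GC-tof-MS, in sensitivity and in specificity against the age-6 diagnosis, with a paired-proportion 95% confidence interval. Keep the per-technique estimates as description.
2. Fix and justify a margin for each before the age-6 diagnoses are known. Claim non-inferiority only if the lower limit lies above minus the margin, and say whether both measures must meet it.
3. Derive both techniques' predictions on the same footing: both algorithms locked beforehand, or both scored out of sample.
4. For the baseline comparison, name the statistic and its criterion, or label it descriptive.

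The cost is analysis work only, with no new measurements. The downside is limited power for sensitivity. If the margin the team can justify is 10 points or less, the hypothesis may be better restated as estimation of the paired difference with its interval.
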